# A multicenter, randomized, parallel-controlled clinical trial protocol to evaluate the safety and efficacy of irreversible electroporation compared with radiofrequency ablation for the treatment of small hepatocellular carcinoma

**DOI:** 10.1186/s12957-024-03614-z

**Published:** 2024-12-20

**Keywords:** Irreversible electroporation (IRE), Radiofrequency ablation (RFA), HCC, Ablation, Protocol

## Abstract

**Background:**

At present, the main clinical application of local ablation therapy, such as radiofrequency ablation (RFA), is to heat the tissue to a certain temperature. However, high temperature will cause thermal damage. Irreversible electroporation (IRE) is a novel minimally invasive local ablation technology for tumors. By high-frequency pulse, the tumor cell membrane can be irretrievably perforated, resulting in the destruction of the intracellular environment, which can preserve important structures in the treatment area. However, there are no randomized controlled clinical trials comparing the efficacy of IRE with traditional local ablation in the treatment of liver cancer.

**Aims:**

This study aims to conduct a randomized controlled clinical trial comparing the efficacy of IRE with RFA in the treatment of liver cancer.

**Methods:**

We will conduct a multicenter, randomized, parallel-controlled non-inferiority clinical trial to compare the efficacy and safety of IRE and RFA for hepatocellular carcinoma (HCC). One hundred and ninety patients with HCC from five academic medical centers will be enrolled. The patients will be randomized into treatment arm (IRE) and control arm (RFA). The primary outcome is the progress -free survival (PFS) and the key secondary outcome is the Overall survival (OS).

**Results:**

Forty-eight patients had been recruited from 5 centers, of which, 33 patients (median age, 59.1 years) with 38 tumors had completed the 1-month follow-up and 21 patients have complete the 3-month follow up, with 2.3 months median follow up period. The mean largest tumor diameter is 3.9 cm. No end point was observed for PFS or OS in both groups, and the complete ablation rate was 100% in both groups. The lesions in the IRE group showed obvious shrinkage 1 month after procedure. One major adverse event (AE) was occurred in the control group.

**Conclusion:**

This is the first randomized controlled clinical trial to compare the clinical effects of IRE and RFA. The preliminary results suggest that both RFA and IRE are effective in the treatment of HCC, which can provide strong evidence for the use of IRE in HCC and provide more options for the treatment of patients with HCC.

**Clinical Trial Registration:**

ClinicalTrials. gov, identifier NCT05451160.

**Supplementary Information:**

The online version contains supplementary material available at 10.1186/s12957-024-03614-z.

## Introduction

Hepatocellular carcinoma (HCC) is the leading cancer in the world, which is ranked top six of the most common cancer and top three of the most common cancer death, with about 500,000 deaths worldwide each year [1]. Its incidence is rising faster than any other cancer [2, 3]. In recent years, percutaneous local ablation has been recognized as a potential treatment for small hepatocellular carcinoma (typically < 3–4 cm), supplemented by surgical resection and liver transplantation [4]. The commonly used ablation methods for HCC are thermal ablation, including radiofrequency ablation (RFA), microwave ablation (MWA), and cryoablation [5]. The goal of thermal ablation is to induce tumor coagulative necrosis at temperatures above 60 °C or below − 40°C [6]. These techniques can ablate tumor tissue and surrounding tissue [7]. However, many tumors cannot be treated with thermal ablation due to their hazardous location. Thermal ablation of tumors near large vessels is associated with a higher incidence of incomplete eradication (heat sink effect) [8–11]. In addition, these modalities can cause thermal damage to vital structures near the ablation area, which can easily lead to serious adverse events [12].

Irreversible electroporation (IRE) is a novel minimally invasive ablation technology for tumors. By high-frequency pulse, the tumor cell membrane can be irretrievably perforated at the nanometer level, resulting in the destruction of the intracellular environment, apoptosis and necrosis. Compared with traditional ablation techniques, it has unique advantages: good tissue selectivity, which can preserve important structures in the treatment area, clear boundaries between the ablation area and non-ablation area, short ablation time, necrosis caused by lack of heat and not affected by thermal/cold desorption of large blood vessels. Its safety and effectiveness have been widely verified in animal experiments [13–15]. Compared with thermal ablation, IRE does not affect the extracellular matrix, thereby maintaining the integrity of blood vessels and bile ducts. In addition, its effect is not affected by temperature changes and is not affected by the “heat sink effect” [16–20]. These characteristics make IRE attractive for the treatment of HCC, especially those at high-risk locations (the mechanisms of RFA, microwave ablation, cryoablation, and IRE are shown in Fig. 1).

**Fig. 1 Fig1:**
[figure not shown]
Mechanisms of local ablative methods for treatment of hepatocellular carcinoma RFA: radiofrequency ablation; MWA: microwave ablation; IRE: irreversible electroporation. This figure was drawn from Figdraw website (https://www.figdraw.com/static/index.html)

IRE has been gradually applied in clinical practice worldwide and is expected to be an effective adjuvant therapy for patients with advanced liver cancer. Previous studies have compared the effects of IRE and RFA, but were all retrospective in nature and nonrandomized prospective study. For example, Thamtorawat et al. [21] retrospectively evaluated 42 patients with HCC who underwent IRE and RFA from January 2014 to September 2020 and compared the efficacy and safety of these treatments. Biliary tract adverse events were found in one (7.7%) patient in the IRE group and five (16.1%) patients in the RFA group. Although the study showed that the safety and efficacy of IRE were greater than those of RFA, it was retrospective in nature, preventing control of the consistency of baseline data between the two groups. Clinical trials comparing radiofrequency and IRE have not yet been reported. Therefore, we conduct a randomized controlled clinical trial to evaluate the efficacy and safety of IRE compared with RFA for HCC ablation.

## Materials and methods

### Study design

This multicenter, randomized, parallel-controlled clinical trial has been registered on ClinicalTrials. gov (NCT05451160), and has been approved by each ethics committee in accordance with the approval procedures of each trial site (the name of relevant ethics committees which provided approval this study and the reference number and year can been seen in the Supplementary Material). All patients entering the trial screening were required to provide written informed consent. The researchers will strictly follow the protocol and good clinical practice requirements to fully protect the legitimate rights, interests, and safety of the participants. This study protocol follows the standard protocol for clinical trials in accordance with the SPIRIT 2013 statement [12] and follows the CONSORT statement for clinical trial transparency [22, 23]. The study protocol conforms to the ethical guidelines of the 1975 Declaration of Helsinki (6th revision, 2008) as reflected in a priori approval by the institution’s human research committee. The flow chart of the study is shown in Fig. 2.

**Fig. 2 Fig2:**
[figure not shown]
Flow chart of the study

### Patient recruitment

The participants will be recruited among patients with hepatocellular carcinoma (HCC) at the First Affiliated Hospital of Zhejiang University School of Medicine, the First Affiliated Hospital of Guangxi Medical University, Zhejiang Cancer Hospital, West China Hospital, Tianjin Third Central Hospital, and Third Affiliated Hospital of Sun Yat-Sen University. Before recruitment, the researchers will introduce the two treatments (Irreversible electroporation (IRE) and radiofrequency ablation (RFA)), including their strengths and limitations, to the participants. Written informed consent will be obtained prior to eligibility screening. Throughout the study, participants could decide to withdraw their consent for any reason. Follow-up results will be disseminated to study participants through written reports and telephone exchanges.

### Patient screening

Eligibility screening will be performed within 14 days before procedure, as shown in Table 1 & Suppl. Table 1.

**Table 1 Tab1:** Follow-up scheme

Trial phase Trial content			a Screening	Follow-up			
			Visit 1	Visit 2	Visit 3	Visit 4	Visit 5
			Preoperative (-14 ~ 0d)	Ablation day (0d)	2 ± 1d after first ablation	30 ± 5d after first ablation	Every 3 months after first ablation
Informed consent^b^			√				
Demographic data			√				
History of liver tumors and past medical history			√				
Vital signs			√	√	√	√	√
Laboratory examination	Urine pregnancy^c^		√				
	Routine urine test^d^		√				
	Routine blood test^e^		√		√	√	√
	Stool routine examination^f^		√				
	Hepatorenal function^g^		√		√	√	√
	Serum electrolyte^h^		√		√	√	√
	Coagulation function^i^		√		√	√	√
	Myocardial enzyme^j^		√		√	√	√
	Tumor marker^k^		√			√	√
Lung CT scan			√				
ECG			√		√	√	√
CEUS			√		√	√	√
Enhanced MRI/CT examination of upper abdomen^l^			√			√	√
ECOG			√			√	√
Child-Pugh			√			√	√
Random allocation				√			
Ablation				√			
Observation of device defects				√			
Evaluation of ablation efficacy						√	√
Record combined medication/treatment			√	√	√	√	√
Handle and record adverse events				√	√	√	√
Verify deviation from protocol				√	√	√	√
Immune index in peripheral blood		The proportion of MDSC ^o^	√	√	√	√	√
		The proportion of TEMs ^o^	√	√	√	√	√
		The concentration of cytokines in serum ^o^	√	√	√	√	√
		Tregs^p^	√	√	√	√	√
		aTregs^r^	√	√	√	√	√
		rTregs^s^	√	√	√	√	√

^(a)^ If the patient has undergone relevant examinations before providing written informed consent and within 14 days before procedure, these data can be collected as data of this clinical trial, and the patient does not need to undergo relevant examinations such as laboratory examination, electrocardiography, and lung CT. The informed process shall be conducted prior to any screening process associated with the trial. ^(b)^ The informed consent process shall be conducted prior to any screening process related to the trial. ^(c)^ Women of childbearing age (18–50 years old and >50 years old without amenorrhea) ^(d)^ Routine urine tests should include at least protein, red blood cell count, and white blood cell count ^(e)^ Routine blood tests should include at least red blood cell count, white blood cell count, hemoglobin, and platelet count ^(f)^ Routine stool tests should include at least occult blood test ^(g)^ Hepatorenal function test should at least include alanine aminotransferase, aspartate aminotransferase, γ−glutamyl transferase, total protein, albumin, total bilirubin, direct bilirubin, blood urea nitrogen or urea, and creatinine ^(h)^ Serum electrolytes should contain at least the following test items: potassium ion, sodium ion, chloride ion, and calcium ion ^(i)^ Coagulation function tests should at least include the prothrombin time, activated partial thromboplastin time, and international normalized ratio ^(j)^ The myocardial enzyme spectrum should at least include phosphocreatine kinase, phosphocreatine kinase isoenzyme, and lactate dehydrogenase ^(k)^ Tumor markers should at least include alpha fetoprotein and carcinoembryonic antigen ^(l)^ Screening MRI/CT examination can still be used within 30 days ^(m)^ Only patients whose first tumor ablation result was “incomplete ablation” should undergo a second ablation, which should be completed within 2 weeks after Visit 4. If Visit 4 and Supplementary visit 1 are completed within the same period of admission, these two visits can be combined as one visit. The inspection performed at Visit 4 is not required for Supplementary visit 1. If not completed within the same admission period, the routine blood and coagulation function tests required at Supplementary visit 1 are available within 14 days before procedure. ^(o)^ These indexes were tested by flow cytometer ^(p)^ Regulatory T cells ^(q)^ Activated regulatory T cells ^(r)^ Resting regulatory T cells CT, computed tomography; ECG, electrocardiography; CEUS, contrast−enhanced ultrasound; MRI, magnetic resonance imaging; CT, computed tomography; ECOG, Eastern Cooperative Oncology Group performance status

The inclusion criteria are as follows:

The patient is 18 to 80 years old, and gender is not limited.Contrast enhanced MRI or CT examination of upper abdomen would be performed. For clinically or pathological diagnosed HCC, the diameter of a single tumor is ≤ 5 cm; for multiple tumors, the number of tumors does not exceed three, and the largest tumor diameter is ≤ 3 cm.The Eastern Cooperative Oncology Group (ECOG) performance status ≤ 2.The liver function classification is Child–Pugh A or B.Life expectancy at least 3 months.The patient is able to understand and comply with the trial protocol and provide written informed consent.

The exclusion criteria are as follows:

Other treatment < 6 weeks prior to treatment.Transcatheter arterial chemoembolization (TACE).Severe infectious disease such as bacteremia or toxemia.Uncorrectable coagulation dysfunction (platelet count of < 40 × l09/L).Lesions abutting main biliary.Severe heart, brain, lung, or other disease, or the patient has severe arrhythmia.Severe coagulation abnormalities.Implanted artificial hearts, lungs, internal pulse regulators, or wearable medical electronic devices such as electrocardiographic monitors.Has a history of epilepsy.Acute myocardial infarction within 6 months.Pregnant or lactating or plans to become pregnant within 1 year.Allergic to ultrasound, CT, or MRI contrast agents.Contraindications to general anesthesia.The patient has participated in a clinical trial of any drug or medical device within the first 3 months of the present study.Other factors that make the patient unsuitable for inclusion or that affect the patient’s participation in the study.

### Ablation procedure

The patients will be randomly divided into trial arm and control arm. The patients in the trial arm will undergo IRE treatment with the steep pulse therapy system produced by Zhejiang Ganevi Medical Technology Co., Ltd. (Zhejiang, China) (Fig. 3A&B). In the control arm, the RFA system produced by Covidien/Medtronic (Fridley, MN, USA) will be used. Before anesthesia, the patient’s basic information will be checked; the contrast-enhanced ultrasound (CEUS) examination findings will be carefully read; and the radiologist will become familiar with the anatomical location, diameter, and number of lesions and then determine the most appropriate needle placement method. The most appropriate position of procedure will be chosen according to liver segment that lesions located in. Both IRE and RFA were performed percutaneous with ultrasound guidance.

**Fig. 3 Fig3:**
[figure not shown]
IRE positioning and IRE machine. (**A. B**) electrodes and equipment of IRE. (**C. D. E**) 2–4 electrodes positioning

#### IRE procedure

After induction of anesthesia, the shape of the ablation area, the number of electrodes, and the needle puncture routes will be designed according to the size and location of the tumor under ultrasound guidance. A 19G monopole electrode needle (Fig. 3A) will be used for the ablation needle, which will have a length of 15 cm, tip exposure of 1 to 2 cm, and needle distance of 1.0 to 2.5 cm. During the puncture process, the radiologist will ensure that the electrodes are parallel to each other and decide whether to perform layered ablation according to the size of the lesion (Fig. 4). The ablation parameters are as follows: voltage, 2500 to 3000 V; 90 to 120 pulses; and wavelength, 70 to 90 us. These parameters will be adjusted according to the intraoperative current rise; the blood pressure, heart rhythm, and muscle spasms will be monitored; and the pulse will be stopped for corresponding treatment when necessary. The images of the patients’ treatment process are shown in the IRE group (Fig. 5A-F). A video of one patient before, during and after treatment is shown in Video 1.

**Fig. 4 Fig4:**
[figure not shown]
Probe position and patient posture during procedure

**Fig. 5 Fig5:**
[figure not shown]
Ultrasound-guided IRE procedure for HCC. (**A**) Pre-ablation contrast-enhanced MRI revealed a hepatocellular carcinoma. (**B&C**) Ultrasound and Contrast-enhanced ultrasound showed a tumor located in S6 (arrow). (**D&E**) Ultrasound-guided IRE with a two-electrode configuration, and the head and tail end of the active tip of the electrodes can have punctuated enhancements (arrow). (**F**) The contrast-enhanced MRI results of one-month after the ablation revealed the tumor shrank obviously and no enhancement after ablation (arrow)

#### RFA procedure

All RFA procedures were performed by interventional radiologists with at least 2 years of experience. Intravenous sedation and local anesthesia were used for patients who could cooperate with procedure, and general anesthesia was used for patients who were tension or other reasons cannot cooperate. An RF electrode manufactured by Covidien/Medtronic (Fridley, MN, USA) was inserted under ultrasonography guidance.

Following the completion of the RFA and IRE, CEUS will be performed to confirm adequate ablation, defined as an ablation zone that includes the entire target tumor and a safe margin of at least 0.5 cm. If insufficient ablation area is suspected, additional energy deposition cycles for overlapping ablation are performed, preferably after electrode pull-back (partial withdrawal of the needle from 1 to 2 cm along the initial puncture axis) and/or partial or complete electrode re-insertion (in a different axis of the initial puncture).

### Follow-up

The efficacy and safety endpoints will be collected 2 ± 1, 30 ± 5, 60 ± 7 days and every three months after the operation, as shown in Table 1 & Suppl. Table 1. This study had one year of enrollment, and the total trial duration was 3 years. The study will end in May 2025, Since the first subjects were recruited in May 2022. At the end of the trial, 2 independent radiologists will review all images before and after treatment, and reach a consensus. Safety assessment is shown in the Supplementary Materials. Preliminary results can be seen in the Supplementary Materials.

### Study outcomes

#### Primary outcome

The primary outcome is to compare the PFS of IRE to RFA for HCC patients.

#### Key secondary outcomes

The key secondary outcome is to compare the OS of IRE to RFA for HCC patients.

#### Other secondary outcomes

Other secondary outcomes are:

30-day complete ablation rate (see Supplementary materials for details evaluation methods).30-day total complete ablation rate (see Supplementary materials for details evaluation methods).The safety of IRE and RFA as measured by the rate and severity of AEs.The efficacy of IRE compared to RFA on:Confirmed Objective Response Rate (ORR);Duration of Response (DoR).

### Adverse events

Adverse events refer to unfavorable medical events that occur during clinical trials, regardless of whether they are related to the therapy. The severity of adverse events will be graded according to Common Terminology Criteria for Adverse Events version 5.0. Possible ablation adverse events are shown in the Supplementary Materials.

### Possible cross overs

For patients who were originally assigned to the RFA treatment group but are not suitable for RFA due to factors such as tumor size and location, we will switch to IRE treatment out of ethics and responsibility for the patients. Similarly, for patients who were originally assigned to the IRE treatment group but are not suitable for IRE and are better suited for RFA, for example patients with implanted artificial hearts, lungs, internal pulse regulators, or wearable medical electronic devices such as electrocardiographic monitors, we will switch them to RFA treatment.

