#### Statistical methods

The statistical description will be performed using the mean, standard deviation, maximum, minimum, median, confidence interval, and rate (composition ratio). For measurement data conforming to a normal or approximately normal distribution, the t-test for two independent samples, repeated-measures analysis of variance, and analysis of covariance will be used for comparison between the two groups, and the paired t-test will be used for comparison between the pretreatment period and each follow-up time point. When the distribution does not conform to a normal or approximately normal distribution, the Wilcoxon rank sum test will be used for comparison between the two groups, and the paired Wilcoxon rank sum test will be used for comparison between the pretreatment period and each follow-up time point. Categorical data will be compared between the two groups using the chi-square test and Fisher’s exact test. McNamar’s chi-square test will be used for comparison between the pretreatment period and each follow-up time point, and the Cochran–Mantel–Haenszel chi-square test will be used for the central effect. The Wilcoxon rank sum test will be used to compare the rank data between the groups. PFS and OS were summarized with the Kaplan-Meier method. mixed-effects Cox models will be used to analyze factors affecting the efficacy. PFS will be based on BICR assessments of tumor assessment and using mRECIST version 1.1. In our final analysis, we will perform the analysis based on intention to treat, full analysis set, Per-Protocol and Safety Analysis Population analysis set. See Supplementary Materials for detailed analysis sets. Analyses were done using R version 4.2.3, an open-source software developed initially in 1993 by Ross Ihaka and Robert Gentleman at the University of Auckland, New Zealand.

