## Discussion

This is the first randomized controlled clinical trial to compare the efficacy and safety of Irreversible electroporation (IRE) with radiofrequency ablation (RFA) for hepatocellular carcinoma (HCC) patients. Although previous studies compared the effects of IRE and RFA and showed that the safety and efficacy of IRE were greater than those of RFA, these studies were retrospective in nature, preventing control of the consistency of baseline data between the two groups [21]. The tumor size was also significantly different between the IRE group and RFA group, which seriously affected the comparability of the results, and the strength of evidence strength provided by the results was therefore low. In contrast, the present study is a randomized controlled trial. The patient inclusion criteria are being strictly implemented, and a randomized method is being used to divide the groups; thus, the baseline data of the trial group and control group will remain consistent, and selection bias will be reduced. We expect that this study will therefore provide strong evidence for the application of IRE in HCC and provide more choices for the treatment of patients with advanced HCC. In this study, the needle will be placed under ultrasound guidance, allowing the process to be observed and adjusted in real time. This method is being used by increasingly more researchers, and its safety and effectiveness have been proven [26, 27].

This study has a larger sample size than that of previous retrospective studies [21, 28]. In addition, this study is a multicenter clinical trial, thus avoiding the selection bias caused by a single-center design and the information bias caused by differences in medical conditions and doctors’ experience levels. Our study design also increases the representation of the enrolled patients, making the results more reliable. We have begun to recruit participants. At the time of this writing, 48 (25.3%) patients had been recruited from 5 centers. The first patient was enrolled on 23 May 2022 and randomly assigned to the IRE group. Thus far, 28 patients have been treated by IRE and 20 patients have been treated by RFA. Among them, 33 patients completed 1 month of follow-up, and all tumors were completely ablated (complete ablation rate of 100%). And no end point was observed for PFS or OS in both groups, which may be due to the current shorter follow-up period. Further follow-up is needed to obtain more reliable results.

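### The plan switches patients between arms after assignment for reasons largely visible at screening, one of them an exclusion criterion; this can bias the non-inferiority comparison, in a direction the documents do not settle

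*Protocol article*

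**What the plan says.** The abstract (Methods) describes a "multicenter, randomized, parallel-controlled non-inferiority clinical trial to compare the efficacy and safety of IRE and RFA". The section Possible cross overs then provides for two switches after assignment:

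- RFA to IRE, for patients "originally assigned to the RFA treatment group but are not suitable for RFA due to factors such as tumor size and location".
- IRE to RFA, for patients better suited to RFA, "for example patients with implanted artificial hearts, lungs, internal pulse regulators, or wearable medical electronic devices such as electrocardiographic monitors".

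The exclusion criteria under Patient screening list "Implanted artificial hearts, lungs, internal pulse regulators, or wearable medical electronic devices such as electrocardiographic monitors". The inclusion criteria set size limits, among them "the diameter of a single tumor is ≤ 5 cm", and state "Contrast enhanced MRI or CT examination of upper abdomen would be performed". Lesions touching the main biliary structure are excluded, so location is also judged at entry. Table 1 puts MRI/CT and contrast-enhanced ultrasound (CEUS) at Visit 1 (days −14 to 0) and random allocation at Visit 2.

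On analysis, Statistical methods says "we will perform the analysis based on intention to treat, full analysis set, Per-Protocol and Safety Analysis Population analysis set" and refers to supplementary material, not shown, for the details.

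**The concern.** Two things look wrong.

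First, the sections conflict. Under the exclusion criteria a patient with one of the listed devices is not randomised. Under Possible cross overs the same patient has been randomised to IRE and is then moved. Both cannot hold.

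Second, the RFA-to-IRE reasons are largely available before allocation. The plan therefore accepts randomising patients whose unsuitability for one arm could have been seen beforehand, then treating them in the other arm. The Discussion states that neither patients nor operators can be blinded, and the section gives no threshold for unsuitability, so the judgement is made with the arm known. The Introduction says that many tumours cannot be treated thermally because of where they lie, so the provision need not be rare.

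What is at stake is the primary comparison. In a non-inferiority trial, mixing treatments can shrink a real difference in the as-randomised analysis, and removing switched patients breaks the randomisation.

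**Working it through.** **Timing and eligibility, side by side**

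| Reason for switch | Where it is known or ruled on |
|---|---|
| Tumour size | Inclusion criterion; MRI/CT and CEUS at Visit 1 |
| Tumour location | Same imaging; one location is an exclusion criterion |
| Implanted or wearable devices | Exclusion criterion, in nearly the same words |
| Random allocation | Visit 2, after all of these |

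**Inputs.** The plan gives no crossover figure to reproduce. Its sample size supplies the event count: 80/0.85 = 94.1, rounded up to 95 per arm and 190 in total, which matches the stated total if 80 is the number before dropout.

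- Events: assume exponential PFS with the stated 7-month median in both arms, 12 months of accrual and 36 months in total. The event probability is 0.946, and 160 × 0.946 ≈ 151.
- Nominal level: one-sided 2.5% (assumed; the article gives α = 0.05 without sidedness).
- Margin M: the article says 20% with no scale. Readings used are HR 1.20–1.25; HR 1.5 as an intermediate value; and HR 1.9, from a 20-point drop in 12-month PFS: 0.5^(12/7) = 0.305, 0.305 − 0.200 = 0.105, and ln 0.105 / ln 0.305 ≈ 1.9.
- Switch rate c: assumed 10% and 20%; the documents give none.

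**Formula.** Let IRE be truly worse by exactly M in every patient, and let switching dilute the log hazard ratio by (1 − c):

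HR_ITT = exp[(1 − c) ln M]

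P(false non-inferiority) = Φ[(ln M − ln HR_ITT) × √151/2 − 1.96] = Φ[c × ln M × 6.144 − 1.96]

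Example, M = 1.5 and c = 0.10: 0.10 × 0.405 × 6.144 = 0.249, and Φ(0.249 − 1.96) = Φ(−1.711) = 4.4%.

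| Margin HR | c = 0 | c = 10% | c = 20% |
|---|---|---|---|
| 1.20 | 2.5% | 3.2% | 4.1% |
| 1.25 | 2.5% | 3.4% | 4.6% |
| 1.5 | 2.5% | 4.4% | 7.2% |
| 1.9 | 2.5% | 5.9% | 12.1% |

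**Check by simulation** (Cox test as randomised, 80 per arm, RFA median 7 months, 4000 runs per scenario). RFA-to-IRE switching alone at 10% and 20% gives 3.7% and 4.6% for margin 1.25, and 5.9% and 10.8% for margin 2.0. At margin 2.0 and 20% the formula gives 13.4%, so it overstates one-way switching at large margins. If the same share of both arms switches, 10% and 20% give 4.3% and 8.8% (margin 1.25), and 17.0% and 45.0% (margin 2.0).

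**When the one-hazard-ratio assumption fails** (simulation, 80 per arm, HR 1.5 in suitable patients, margin 1.5, 20% unsuitable for RFA). If unsuitable patients have assumed relative hazards of 1.5 on IRE and 2.25 on RFA, switching lowers the chance of claiming non-inferiority from 13.4% to 6.5%. With those two hazards reversed, it rises from 2.8% to 5.6%.

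**Per-protocol.** If RFA-unsuitable patients have 1.5 times the hazard (assumed) and are dropped from the RFA arm only, a true HR of 1.25 appears as 1.29 (10% dropped) or 1.34 (20%). False non-inferiority falls to 1.4% or 0.8%.

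**The case against.** The strongest objection is that the direction of bias is conditional. The table applies one hazard ratio to everyone, including patients judged unsuitable for RFA. The Introduction argues that thermal ablation near large vessels leaves more residual tumour and that IRE escapes the heat-sink effect. If so, switching improves the results of the RFA arm and makes non-inferiority harder to claim, as the simulation shows. Under the planning hazard ratio of 0.347 the observed ratio also moves against IRE, to about 0.44 at 10% switching and 0.55 at 20%, although non-inferiority against 1.25 still succeeds in at least 99% of runs. This objection stands. A reader might infer that the provision simply makes non-inferiority easier to claim; the documents do not support that as a general statement.

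Four other stronger readings also fail:

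- That no analysis set guards the conclusion. Dropping difficult tumours from the RFA arm alone would tend to count against IRE, so per-protocol is biased but not necessarily in IRE's favour.
- That the plan leaves the decisive analysis set open. The details are deferred to a supplement not shown.
- That switching is mainly one-way. The devices are only an example; other reasons for IRE unsuitability are not excluded.
- That switching is already visible because "28 patients have been treated by IRE and 20 patients have been treated by RFA". Under 1:1 allocation a split at least this uneven has two-sided p = 0.31, and the counts are by treatment received.

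It is also fair to say that some unsuitability may emerge only at the procedure. A rule for such cases is reasonable, but it does not explain a provision resting on size, location and devices.

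**Conclusion.** The point holds in this form. Possible cross overs contradicts the device exclusion, and it plans switches after assignment for reasons largely visible before it. Both follow from the text and need no assumption.

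The consequence is a possible bias whose size and direction are uncertain. If IRE is uniformly worse by the margin, the as-randomised false non-inferiority rate exceeds the nominal 2.5%: modestly on the HR 1.20–1.25 reading (3.2–4.6% across 10–20% switching), and up to 12.1% at HR 1.9. These figures rest on 151 events, one-sided 2.5%, an assumed switch rate, an assumed margin scale and a single hazard ratio for all patients. If switched patients would do better on IRE, the bias runs the other way. Per-protocol analysis is no clean substitute, because the direction of its bias depends on the prognosis of those removed.

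**What to change.** 1. Before random allocation, have the treating team confirm from screening imaging and history that the patient and every target lesion are suitable for both IRE and RFA. Log the others as screen failures and do not randomise them.
2. Reconcile Possible cross overs with the device exclusion under Patient screening.
3. For any switch that still occurs, leave care to the investigator, analyse the patient in the randomised arm, and report switches with reasons by arm.
4. Claim non-inferiority only if the as-randomised and per-protocol analyses agree.

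Cost: a protocol amendment at each site (each has its own ethics approval), a screening-form item, a few more screen failures and a slightly narrower population. The 48 patients already recruited at the time of writing entered under the existing criteria, so a sensitivity analysis should address that difference.
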